- Objective sleep substudy: to investigate the difference between objective sleep measures (as measured by Dreem-3 EEG-headband and Withings Sleep Analyzer) and subjective sleep measures (as measured by the Richard Campbell Sleep Questionnaire and the Consensus Sleep Diary) for a population of hospitalized medical and surgical patients
- Objective sleep substudy: to investigate the association between quality of recovery and objective sleep quality and sleep-wake timing
- Objective sleep substudy: to investigate the association between 30-day mortality and objective sleep quality and quantity
- Objective sleep substudy: to investigate the association between 30-day incidence of delirium and objective sleep quality and quantity
- Objective sleep substudy: to investigate the association between the 30-day incidence of surgical site infections and objective sleep quality and quantity (for surgical patients)

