# STUDY DESIGN

In this cluster randomized controlled trial, performed in both locations of the Amsterdam University Medical Centre, we will randomize 6 surgical and 6 medical departments to either standard care group (SG) or WEsleep intervention group (WI). All adult patients admitted to the participating departments will receive the sleep improving interventions during their admission, informed consent will be obtained for sleep assessment.

Implementation of the interventions will be evaluated on a regular basis throughout the length of the study to make sure that all interventions are provided to our patients as planned. Before implementation, a baseline measurement will be conducted on all participating departments in a small number of patients (which is not part of the sample size). We observed that some interventions were gradually implemented. As such, we decided that for optimal assessment of the effect of the intervention a run-in period of 12 weeks before starting assessment of the primary and secondary outcomes would be reasonable. Sleep measurements between study onset and outcome will be used to guide implementation and will be reported in eventual journal articles.

After 12 weeks (that is, after July 1st), 33 patients per participating department will be included, for a total of 396 patients (12 departments with 33 patients each) and analyzed for the outcomes of the study. Informed consent for sleep measurements will be obtained on the first or second day of admission into one of the participating wards. Patients will be followed until discharge or for a maximum of 7 nights of admission. Patient characteristics, as well as data on the admission will be extracted from the electronic medical record. Patients will be asked to complete two questionnaires daily: Richards Campbell Sleep Questionnaire (RCSQ) on subjective sleep quality and the Consensus Sleep Diary (CSD) for day-to-day sleep wake timing. Furthermore, patients are asked at admission to complete the two questionnaires on sleep quality and sleep-wake timing on work- and work-free days (RCSQ and CSD) retrospectively, i.e. for 30 days before admission. Surgical patients will also complete a Quality of Recovery 15 (QoR-15) questionnaire twice (once at one day after surgery/first day of admission and once three days after surgery/third day of admission).

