In the separate objective sleep substudy, 24 patients will be recruited from each group (medical intervention and control groups, surgical intervention and control groups), for a total of 96 patients. Measurements between April 11th and June 30th will be used to guide implementation of interventions. Patients included after July 1st will be analyzed for the outcomes of the substudy. Informed consent for the substudy will be obtained separately at the same time as consent for the main study. All patients participating in the main study will be asked to participate in the substudy as well. After obtaining consent, a lottery system will decide which patients can participate in the substudy (due to the scarcity of available Dreem-3 EEG headbands and Withings Sleep Analyzers).

In the substudy, objective sleep in patients will be measured with the Dreem-3 EEG-headband and the Withings Sleep Analyzer. The Dreem-3 headband uses electro-encephalography (EEG) and a validated algorithm to differentiate between wakefulness and various sleep stages (Rapid-Eye Movement (REM)-sleep and non-REM N1, N2 and N3 sleep) and the time at which these occur. The Withings Sleep Analyzer can be placed under the mattress and uses measurement of movement to differentiate between wakefulness and light, deep and REM-sleep and the times at which these occur.

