# METHODS

## Study parameters/endpoints

### Main endpoint

Our primary outcome is the subjective sleep quality as measured the Richards-campbells sleep questionnaire.

Subjective sleep quality will be assessed with the Richard Campbell Sleep Questionnaire (RCSQ). The RCSQ measures sleep quality on five questions using a visual analogue scale (VAS), ranging from 0 to 100, with higher scores indicating a better sleep quality. A sixth question was added to assess noise levels (as is quite customary), using a VAS-scale, ranging from 0-100, with a higher score indicating more noise.

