Objective sleep substudy:

- Sleep efficiency (objectively measured) during admission. Objective sleep quality will be measured by the Dreem-3 headband, using electro-encephalography (EEG) to differentiate between wakefulness, Rapid-Eye-Movement (REM) sleep and non-REM N1, N2 and N3 sleep. The primary outcome measure will be sleep efficiency (time slept divided by time in bed spent trying to sleep), compared for patients on intervention and control departments.
- Differences in objective sleep measures of sleep-wake timing during admission. Changes in sleep-wake timing (i.e. midpoint of sleep, sleep on- and offset time, sleep duration, sleep latency & inertia) will be compared for patients on intervention and control departments.
- Night-to-night changes in objective sleep measures during admission. The amount of time in each of the different sleep stages and their distribution, as well as total sleep time, will be compared for patients on intervention and control departments.
- Difference between objective and subjective sleep measures during admission. Subjective sleep measured with the RCSQ and CSD.
- Quality of recovery after surgery and objective sleep quality/timing.
- Correlation 30 day mortality and objective sleep quality/timing.
- Correlation 30-day incidence of delirium during admission and objective sleep quality/timing.
- Correlation 30-day incidence of surgical site infections (for surgical patients) and objective sleep quality/timing.

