- Difference between objective and subjective sleep measures during admission. Subjective sleep measured with the RCSQ and CSD. This will be evaluated by looking at the association between objective and subjective sleep by performing linear regression.
- Quality of recovery after surgery and objective sleep quality/timing. This will be evaluated by performing linear regression.
- Correlation 30 day mortality and objective sleep quality/timing. This will be evaluated by performing linear regression.
- Correlation 30-day incidence of delirium during admission and objective sleep quality/timing. This will be evaluated by performing linear regression.
- Correlation 30-day incidence of surgical site infections (for surgical patients) and objective sleep quality/timing. This will be evaluated by performing linear regression.

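### The substudy sets out to measure the difference between device-recorded and self-reported sleep, but the only planned analysis is a regression for association, which does not commit to estimating that difference

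*Protocol*

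**What the plan says.** Under Secondary Objectives, the substudy is "to investigate the difference between objective sleep measures (as measured by Dreem-3 EEG-headband and Withings Sleep Analyzer) and subjective sleep measures", the subjective side being the RCSQ and the CSD. Under Secondary endpoints the item reads "Difference between objective and subjective sleep measures during admission. Subjective sleep measured with the RCSQ and CSD". Section 10.2, Secondary study parameter(s), repeats that heading and then fixes the method: "This will be evaluated by looking at the association between objective and subjective sleep by performing linear regression". No paired difference, bias estimate or measure of agreement is planned for this item anywhere in the protocol.

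The two subjective instruments are on different footings. The RCSQ is a visual analogue score "ranging from 0 to 100, with higher scores indicating a better sleep quality" (Main endpoint), which has no counterpart in device units. The Study Design section gives the "Consensus Sleep Diary (CSD) for day-to-day sleep wake timing", and the secondary endpoints list midpoint, onset, offset, duration and latency from it. The substudy endpoints list those same five quantities as device measures.

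The substudy recruits four groups of 24, "for a total of 96 patients". On follow-up: "Patients will be followed until discharge or for a maximum of 7 nights of admission".

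**The concern.** A difference between two measurements of the same night in the same patient is one question, and whether the two rise and fall together is another. A regression for association answers the second. If hospitalised patients as a group report an hour more sleep than the headband records, the association can be strong while the quantity named in the objective goes unreported.

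The wording does not look accidental. The four substudy objectives that follow this one (quality of recovery, mortality, delirium, surgical site infection) are all phrased as associations; only this one is phrased as a difference. In section 10.2 the other within-patient differences, hospital versus home sleep quality and the shift in sleep midpoint, are given a paired t-test, and the items called associations with food timing and quality of recovery are given regression. Here a difference has been given the association method. Because the protocol names that method, this is not a detail left open for a statistical analysis plan.

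At stake is whether the substudy answers one of its own stated questions from data it will already hold.

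**Working it through.** The protocol gives no sample size, power or effect for this comparison, so there is no figure to reproduce. The check is algebra plus a simulated illustration.

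**Algebra.** Let x be the device value and y the diary value, with fitted line y = a + b·x. Replace every y by y + d:
- b = cov(x, y)/var(x) does not change, because a constant alters neither term.
- The residuals do not change, so R-squared and the p-value for b do not change.
- a becomes a + d.
- The mean paired difference becomes (ȳ - x̄) + d.

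A shared offset is therefore invisible to the association and moves only the intercept.

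**Inputs.** From the protocol: 4 × 24 = 96 patients. Assumed, because the protocol gives no values: one pair per patient, device sleep duration with mean 360 and SD 75 minutes, random reporting error with SD 0, 20, 45 or 75 minutes, and a shared offset of 0 or 60 minutes.

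| Error SD (min) | Offset (min) | Slope | R-squared | Intercept (95% CI) | Mean difference (95% limits of agreement) |
|---|---|---|---|---|---|
| 0 | 0 | 1.000 | 1.000 | 0 | 0 (0 to 0) |
| 0 | 60 | 1.000 | 1.000 | 60 | 60 (60 to 60) |
| 20 | 0 | 0.971 | 0.916 | 8.9 (-12.9 to 30.7) | -1.3 (-38.8 to 36.3) |
| 20 | 60 | 0.971 | 0.916 | 68.9 (47.1 to 90.7) | 58.7 (21.2 to 96.3) |
| 45 | 0 | 1.084 | 0.730 | -39.2 (-87.9 to 9.6) | -9.3 (-93.5 to 74.9) |
| 45 | 60 | 1.084 | 0.730 | 20.8 (-27.9 to 69.6) | 50.7 (-33.5 to 134.9) |
| 75 | 0 | 0.895 | 0.428 | 37.1 (-39.4 to 113.7) | -0.1 (-131.8 to 131.7) |
| 75 | 60 | 0.895 | 0.428 | 97.1 (20.6 to 173.7) | 59.9 (-71.8 to 191.7) |

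Within each pair of rows the slope and R-squared are identical and the mean difference moves by 60. Means such as 50.7 differ from 60 through the random error drawn in that sample.

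**How good is the intercept as an estimate of bias?** With true slope 1 and error SD σ:
- SE(mean difference) = σ/√96. At σ = 45: 45/9.798 = 4.59 minutes.
- SE(intercept) = σ·√(1/96 + 360²/(95·75²)). At σ = 45: 45·√(0.0104 + 0.2425) = 45 × 0.503 = 22.6 minutes.
- Ratio: 22.6/4.59 = 4.9, whatever σ is.

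A 60-minute offset is thus 60/4.59 = 13.1 standard errors for the paired difference but 60/22.6 = 2.7 for the intercept. In 2000 simulated trials per setting, the intercept's 95% CI lay above 0 in 100%, 73% and 33% at error SD 20, 45 and 75; the paired test detected the offset in 100% at all three.

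**Other error patterns**, without random error:
- Every diary value 1.3 times the device value: R-squared 1.000, mean difference 106.6 minutes. The slope of 1.3 does show this.
- Half the patients at +60 and half at -60: R-squared 0.532, mean difference 0.0, limits of agreement -118.2 to 118.2.
- One patient of 96 at +60: R-squared 0.991, slope 1.005, mean difference 60/96 = 0.6.

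**The case against.** The strongest reply is that a fitted line contains more than a slope and an R-squared. Its intercept moves one for one with a shared offset, and since a least-squares line passes through both means, the mean difference can be recovered as a + (b - 1)·x̄. This stands, so it would be wrong to say the regression output is the same whatever the offset. But the protocol plans to look at the association, says nothing of interpreting the intercept, and the intercept on its own is about 4.9 times less precise than the paired difference under the assumptions above. Recovering the difference by hand from the fit is not a planned estimate with an interval, and it gives no limits of agreement.

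A reader might go further and infer several things that the protocol does not support:
- *That a biased device would be reported as agreeing fully with patients.* The text promises an association and never says it will be presented as agreement.
- *That a single patient who misreports by an hour would go unseen.* In a pooled regression, offsets that differ between patients are scatter and lower R-squared (0.532 with half at +60 and half at -60). Only an offset common to all is invisible to the association.
- *That this decides how the primary outcome may be read.* The primary outcome is the RCSQ, which has no device unit, and regression is a suitable analysis for it.

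It can also be said that this is one descriptive item in a substudy, involves no randomised comparison, and could be repaired at analysis. That limits its weight but does not remove the mismatch.

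**Conclusion.** The point holds for the CSD quantities that share units with the devices: onset, offset, midpoint, latency and duration. For these, the objective and endpoint name a difference and section 10.2 plans only an association, so the plan does not commit to estimating what it set out to estimate. An over- or under-report of any size shared by all patients would leave the slope, R-squared and p-value as they were.

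The invariance is exact and needs no assumptions. The figures for the intercept's imprecision rest on assumed values (device mean 360, SD 75, error SD 20 to 75 minutes, one night per patient) and would change with others.

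The point does not extend to the RCSQ. It concerns a secondary substudy objective and leaves the primary analysis untouched. It is worth correcting because a stated question would otherwise go unanswered.

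**What to change.** In section 10.2, split this item in two.

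1. For sleep onset, offset, midpoint, latency and duration from the CSD, analyse the paired difference diary minus device. Report the mean difference with its 95% CI and the 95% limits of agreement, separately for the headband and the mattress sensor. Allow for repeated nights within a patient, for example with a patient random effect: with at most 7 nights there can be up to 96 × 7 = 672 pairs per device, and they are not independent. Include sleep efficiency only if the diary yields it; the protocol describes it for the headband and does not list it among the CSD quantities.
2. For the RCSQ, keep linear regression, and reword the matching part of the objective and endpoint as an association.

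The cost is a change of wording and a little more analysis of data the protocol already plans to collect. Recruitment, measurements and the primary analysis stay as they are.

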# ETHICAL CONSIDERATIONS

## Regulation statement

The study will be conducted according to the principles of the Declaration of Helsinki 2004 (amendment Fortaleza, Brazil, October 2013) and in accordance with the Medical Research Involving Human Subjects Act (WMO) and CCMO/ICH GCP guidelines.

## Recruitment and consent

Patients admitted into one of the participating departments who meet inclusion criteria will be asked if they are willing to participate in the evaluation of the intervention at the first day of hospital admission (or as soon as possible, if recruitment cannot take place on the first day (e.g. admission in the weekend)). Patients will be recruited after informed consent has been obtained.

## Objection by minors or incapacitated subjects

No minors or incapacitated subjects will be included in this study.

## Benefits and risks assessment, group relatedness

Patients admitted into the participating departments that are randomized for intervention will have the possible benefits of the interventions aimed at an improved sleep quality and minimal disruption of the circadian timing system. All interventions are very low-risk, as they are intended to be easily implemented and applied.

Patients admitted into control departments will receive standard care and will have no additional benefits or risks associated with the study.

## Compensation for injury

The sponsor/investigator has a liability insurance which is in accordance with article 7 of the WMO. The sponsor (also) has an insurance which is in accordance with the legal requirements in the Netherlands (Article 7 WMO). This insurance provides cover for damage to research subjects through injury or death caused by the study.

The insurance applies to the damage that becomes apparent during the study or within 4 years after the end of the study.

# ADMINISTRATIVE ASPECTS, MONITORING AND PUBLICATION

## Handling and storage of data and documents

The data of each patient will be noted on an individual case report form (electronic Case Report Form (CRF). All data of each patient will be noted on an individual case report form. Data will be coded using a numerical code, the key to this code is only available to the research team and is stored in the investigator site file in accordance with the Dutch law ‘Wet Bescherming Persoonsgegevens’ (WBP; Personal Data Protection Act) and GCP. All patient data will be handled confidentially and anonymously. Data will then be inserted into a database (GCP validated), and correctness of entries will be controlled by a second investigator. All data, including case report forms, trial master file, investigator site file and consent forms will be stored for 15 years after completion of the study. Data, both anonymous (e.g. CRFs) or not (e.g. source documents), will always be stored securely, in a locked cabinet (hard copy) or on password secured computers.

## Monitoring and Quality Assurance

Monitoring will be performed according to Dutch Federation of University Medical Centre norms, NFU 2.0). A detailed monitoring plan will be drafted, which involves an initiation visit and subsequent yearly monitoring visits for each site involved. Monitoring is performed by the Clinical Research Unit (CRU, according to Dutch Federation of University Medical Centre norms, NFU 2.0). In addition, the study can be subjected to internal and external auditing.

## Amendments

A ‘substantial amendment’ is defined as an amendment to the terms of the METC application, or to the protocol or any other supporting documentation, that is likely to affect to a significant degree:

- the safety or physical or mental integrity of the subjects of the trial;
- the scientific value of the trial;
- the conduct or management of the trial; or
- the quality or safety of any intervention used in the trial.

All substantial amendments will be notified to the METC and to the competent authority.

Non-substantial amendments will not be notified to the accredited METC and the competent authority, but will be recorded and filed by the sponsor.

## Annual progress report

The sponsor/investigator will submit a summary of the progress of the trial to the accredited METC once a year. Information will be provided on the date of inclusion of the first subject, numbers of subjects included and numbers of subjects that have completed the trial, serious adverse events/ serious adverse reactions, other problems, and amendments.

## Temporary halt and (prematurely) end of study report

The sponsor will notify the accredited METC and the competent authority of the end of the study within a period of 90 days. The end of the study is defined as the last patient’s last visit.

The sponsor will notify the METC immediately of a temporary halt of the study, including the reason of such an action.

In case the study is ended prematurely, the sponsor will notify the accredited METC and the competent authority within 15 days, including the reasons for the premature termination.
Within one year after the end of the study, the investigator/sponsor will submit a final study report with the results of the study, including any publications/abstracts of the study, to the accredited METC and the Competent Authority.

## Public disclosure and publication policy

There are no publication disclosures. The data will be presented on national and international congresses and will be published in a peer reviewed international journal.

# STRUCTURED RISK ANALYSIS

There are no risks associated with the study.

